### Interventions

#### Study procedure

Enrolled patients will be treated with CT-guided SBRT on a standard, gantry-mounted LINAC (Arm 1) or with MRI-guided SBRT (Arm 2) on an MRI-guided LINAC (MRIdian System™, ViewRay™, Cleveland, OH, USA).

#### Radiation simulation planning and dosage

Enrolled patients will undergo CT simulation and planning as per routine for patients. Patients will be provided a bladder filling protocol with instructions to void one hour prior to simulation (and prior to each treatment), and drink at least two eight-ounce glasses of water. Patients will also be asked to perform a Fleet enema the night before and morning of their simulation scan. At the time of simulation, a custom VacLoc bag, alpha cradle, or equivalent device will be used for patient immobilization and establishment of treatment geometry. A pelvic CT without contrast will be performed for radiotherapy simulation (i.e., treatment planning CT) with a slice thickness of 1.5 mm. For patients enrolled on the MRI-guided SBRT arm, an additional MRI will be obtained in the treatment position on the MRI-guided LINAC.

Implanted fiducial markers are routinely used to assist with motion management when treating prostate cancer patients with any form of external radiotherapy, including SBRT [27]. These will be considered required for patients treated with CT-guided SBRT except in cases where a medical contraindication is present, as is consistent with our internal SBRT protocol. For patients being treated with MRI-guided SBRT, since the prostate can be visualized with the real-time cine feature, implanted fiducial markers will not be required. The use of a hydrogel is not an exclusion criterion for the trial, but is not considered mandatory either.

#### Radiotherapy contouring and planning

The entire prostate will be contoured as the CTV_P_. The proximal 1 cm of seminal vesicles will also be included in the CTV_P._ for patients with intermediate and high-risk disease. For patients with cT3a disease (i.e. extracapsular disease), the CTV_P_ will be expanded to cover the radiographic extent of ECE. For patients with cT3b disease, the CTV_P_ will be expanded to cover the entire seminal vesicle. The CTV_P_ will be expanded by 2–5 mm isotropically (typically 4 mm isotropically for CT-guided arm, per recent data from our institution [28] and 2 mm isotropically for the MRI-guided arm). Note the posterior expansion can be smaller than the expansion in other directions, i.e. the posterior expansion can be anisotropic with respect to the other expansions) to form the PTV_P._ We adopted a smaller margin of 2 mm for the MRI-guided arm given its ability for real-time tracking and superior prostatic anatomy visualization (i.e., greater contour certainty), with little concerns of marginal misses related to excess motion or undercontouring. For selected patients with high-risk disease, whole pelvic radiotherapy (WPRT) can be considered. If WPRT is to be delivered, the obturator, presacral, internal iliac, and external iliac nodal stations will be considered as targets. The nodal CTV (CTV_N_) will be defined as per the RTOG consensus guidelines [29]. CTV_N_ will be expanded isotropically by 4 mm to form PTV_N_.

Prescription doses for PTV_P_ and PTV_N_ are shown in Fig. 1. For all PTVs, the prescription dose will be prescribed such that 95% of the PTV receives at least the prescription dose, unless doing so would lead to violation of the organ-at-risk (OAR) dose constraints listed in Additional file 1. In such cases, undercoverage of either the PTV_P_ or the PTV_N_ will be allowed per physician discretion.

#### OAR doses

OAR doses are listed in Additional file 1. Doses that exceed the constraints below will be considered deviations from the protocol and can be delivered if study investigators agree that the deviation is acceptable and unlikely to cause excessive morbidity.

#### Radiation treatment delivery

The same patient immobilization, bladder filling and bowel preparation protocol for simulation will be employed during treatment delivery. Before each fraction of radiation treatment delivery, a 1.5 mm isotropic voxel size or better high resolution breathing scan will be taken with the on-board MRI to delineate the geometry of the target and OAR. If deemed necessary, online adaptive planning will be performed, wherein the planning GTVs, CTVs, and OARs are deformably transferred to the online MR images via registration, and the treatment plan is reoptimized to meet or exceed the original planning goals. Gating-based treatment, with gating based on the imaged location of the prostate organ or on rectal distention, can be employed at the discretion of the treating physician. Treatments will be delivered every other day, or consecutive days if necessary, with all fractions to be delivered within a period not exceeding 14 consecutive chronologic days.

#### Hormonal therapy (HT)

HT will be delivered at the discretion of the treating physician. Per the NCCN guidelines [3], HT is recommended at a duration of 4–6 months for unfavorable intermediate-risk prostate cancer or 12–36 months for high-risk prostate cancer (with 12–36 months in the context of extremely dose-escalated radiotherapy, and 18–36 months for standard dose-escalated radiotherapy). HT generally consists of combined androgen blockade, which is comprised of (a) a luteinizing hormone-releasing hormone agonist (e.g. leuprolide) or a gonadotropin-releasing hormone antagonist (e.g. degarelix) and (b) an oral anti-androgen (e.g. bicalutamide). In combined androgen blockade, the anti-androgen is generally given for one to six months. Given the emerging roles of advanced anti-androgen agents, particularly in high-risk disease [30], enhanced HT agents may also be given per physician discretion.

### Follow-up and adherence to interventions

Patients will be evaluated at their initial encounter (baseline/pre-treatment), at 1 month post-SBRT, at 3 months post-SBRT, and then every 3 months for the first year after treatment, and then every 6 months for a minimum of 5 years after treatment (+/− 4 weeks). After 5 years have elapsed, patients will be evaluated on an annual basis (+/− 4 weeks). Visits after 3 months, or at any timepoint at which the investigator believes it is in the best interest of the subject, may be performed remotely. No ancillary or post-trial care procedures are specified per the protocol.

### Physician scored toxicity

All acute and late adverse events from protocol radiation therapy will be reported and scored for severity using the CTCAE version 4.0.3. The same toxicity scale will be used for both acute and late radiation adverse events.

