MRI-guided linear accelerator (LINAC) systems, which have just recently become commercially available, offer several technical advantages that can minimize the planning margins needed for SBRT. First, these devices can monitor prostate motion in real-time, abrogating the need for implanted fiducials and eliminating the need for frequent X-ray based imaging to detect these fiducials. The precise visualization of boundaries between the prostate and nearby important healthy tissues such as the bladder and rectum from the MR images also allows for narrower margins. Second, the prostate is seen more clearly on MRI than on CT-based imaging, such that prostate target volumes generated by MRI are smaller and more reproducible than those generated by CT [22]. While MRIs can guide the generation of CT-based contours through image fusion, the fusion process itself introduces 1–2 mm of residual error [23]. Treatment on an MRI-based device, which itself has significantly improved soft-tissue contrast, allows for more accurate target delineation by bypassing the need for CT-MRI fusion. Finally, the adjacent critical structures are highly deformable and, despite rigorous patient preparation instructions, will lead to anatomic variability from fraction to fraction. Such deformation cannot be corrected using fiducial marker-based translational and rotational corrections on a conventional LINAC with x-ray image guidance. Daily cone-beam CT (CBCT) is not well equipped for this task either due to poor organ visualization. Modern MRI-guided LINAC systems can uniquely correct for these deformations using online adaptive radiotherapy, wherein a new radiotherapy plan is generated on the basis of the anatomy seen at a given fraction [24]. PTV margin, even by 1–2 mm, has a dramatic impact on PTV volume. For instance, for a spherical target with radius ~ 2.28 cm, the volume is 50 cc. A 4 mm PTV margin would lead to a volume of 81 cc, compared with 64 cc for a 2 mm PTV. Considering the majority of the excess PTV will be affecting the bladder wall and rectum, this difference is considerable.

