#### Primary endpoint

The incidence of acute grade ≥ 2 GU physician-reported toxicity, as assessed by the CTCAE version 4.03 scale. The timeframe will be restricted to the first 90 days after SBRT.

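### Fiducial implantation is required in the CT arm only, and an implantation-related event that resolves before SBRT enters no stated endpoint, so the safety comparison of the two strategies is incomplete.

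*Protocol article*

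**What the plan says.** **Arms.** Under Radiation simulation planning and dosage, the protocol article says of fiducial markers in the CT arm: "These will be considered required for patients treated with CT-guided SBRT except in cases where a medical contraindication is present". For the MRI arm, "implanted fiducial markers will not be required"; they are not prohibited there. The same section leaves a hydrogel spacer optional in either arm. The Background describes MRI-guided devices as "abrogating the need for implanted fiducials and eliminating the need for frequent X-ray based imaging".

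**Reporting scope.** The section Physician scored toxicity states: "All acute and late adverse events from protocol radiation therapy will be reported".

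**Endpoint and window.** The Primary endpoint section defines "The incidence of acute grade ≥ 2 GU physician-reported toxicity, as assessed by the CTCAE version 4.03 scale" and adds: "The timeframe will be restricted to the first 90 days after SBRT". The Secondary endpoints section sets the same window for acute GI toxicity. Neither definition restricts events by cause.

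**Schedule.** Table 2 (Study calendar) asks for one pre-treatment toxicity and QOL assessment, either up to 4 months before radiotherapy or on SBRT day 1. It marks none during the five fractions, and the next is at 1 month.

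**Blinding.** The section on selection, enrolment and randomization says that the trial is open label and that outcome assessors know the assignment.

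**The concern.** The trial randomizes between two ways of guiding SBRT, and one of them normally includes an invasive step before treatment that the other does not need. Reporting is scoped by cause, to radiation therapy, and the acute endpoints are scoped by time, to the period after SBRT. Harm from the invasive step can fall outside both.

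Two things are at stake. First, the safety comparison may leave out harm that arises mainly in one arm, so it would describe toxicity after radiation and not the full burden of each strategy. Second, the reporting rule and the primary endpoint can give different answers for the same early post-SBRT GU event in an implanted patient. The deciding judgment is then one of cause, made by someone who knows the arm.

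**Working it through.** **1. Following an event through the sections**

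| Event in an implanted patient | Endpoint definition (Primary and Secondary endpoints) | Reporting scope (Physician scored toxicity) | Result |
|---|---|---|---|
| Starts and resolves before SBRT | Outside the window | Not from radiation therapy | In no stated endpoint; at most seen as baseline status |
| GU, grade ≥2, starts before SBRT and persists after it | Can be met, since no cause is specified | Not clearly covered | The two sections differ |
| GU, grade ≥2, starts soon after SBRT, cause uncertain | Met | Covered only if attributed to radiation | Depends on an unblinded judgment |
| Infectious event not graded as GU or GI | Not an endpoint event | Not clearly covered | In no stated endpoint |

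The first row follows from a stated scope and a stated window, and not merely from silence.

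**2. The plan's own figure**

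Inputs from the Sample size section: 29% (CT) against 15% (MRI), 150 per arm, one-sided α = 0.025, two-sample Z-test.

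- Pooled proportion: (0.29 + 0.15)/2 = 0.22
- SE under the null: √(0.22 × 0.78 × 2/150) = 0.0478
- SE under the alternative: √((0.29 × 0.71 + 0.15 × 0.85)/150) = 0.0471
- Power: Φ((0.14 − 1.96 × 0.0478)/0.0471) = Φ(0.98) = 0.837

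The stated 83.7% is reproduced. It depends on the assumed rates for the defined endpoint, and nothing in this point changes it.

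**3. Direction**

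An uncounted event that arises mainly in CT patients lowers the counted CT rate and narrows the observed difference. The error therefore runs against the MRI arm. It cannot produce a false claim of MRI superiority.

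**4. Illustration of size, on assumed rates only**

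The article gives no rate of harm from implantation. Let h be an assumed rate of grade ≥2 implantation events, with all 150 CT patients implanted and no MRI patients, and with h independent of radiation toxicity. Expected patients with such an event = 150h. The CT rate with these events added = 0.29 + 0.71h.

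| Assumed h | Expected patients of 150 | CT rate with h added | Difference from 15% | Power if all were counted |
|---|---|---|---|---|
| 0.5% | 0.75 | 29.4% | 14.4 points | 85.3% |
| 1% | 1.5 | 29.7% | 14.7 points | 86.8% |
| 2% | 3.0 | 30.4% | 15.4 points | 89.4% |
| 5% | 7.5 | 32.6% | 17.6 points | 95.0% |

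The last three columns also suppose that every such event is GU and is counted in the endpoint. They show direction only. They are neither an estimate nor an argument for moving the endpoint window.

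**The case against.** The strongest reply is that the endpoint answers the question the article asks. The Abstract and Objectives concern toxicity after SBRT, and a comparison of all harm from each strategy is a different quantity. That stands, and it is why the primary endpoint and its window should stay as they are.

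Several stronger readings are tempting, and the documents do not support them:

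- *Implantation harm is never counted.* The primary endpoint has no attribution clause, so GU harm persisting after SBRT can meet it. The reporting sentence does not literally say that only radiation events are reported. The Early stopping guidelines refer to grade ≥3 GU and GI events without limiting them to radiation.
- *The trial fails to test a benefit it claims.* Avoiding fiducials is listed as a technical advantage tied to visualization and margins. No section claims fewer implantation complications.
- *The CT arm's baseline is contaminated.* Allocation is not released until screening and baseline data are entered, and baseline IPSS is a stratification factor, so that score precedes any implantation prompted by allocation. Table 2 does allow the toxicity and QOL assessment on SBRT day 1, so a later baseline is possible. The article does not say when fiducials are placed or that late baselines are the practice.
- *The contrast is implant against no procedure.* CT patients with a contraindication are exempt, MRI patients may have fiducials, and a hydrogel spacer is open to both arms.

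It can also be said that this is a condensed article and that the full protocol, which is not shown, may provide for procedural events. It may. But the article does more than stay silent: it states a reporting scope, and procedural events fall outside that scope.

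**Conclusion.** The point holds in a limited form. An implantation-related event that starts and resolves before SBRT is in no stated endpoint, and the procedure that could cause it is required in one arm only. For early post-SBRT GU events, the reporting scope and the primary endpoint do not agree on whether cause matters, and assessors are unblinded.

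A reader might infer that the primary result would be invalid. It would not be: the omission is conservative for MRI superiority and the stated power stands. What is lost is completeness and even-handedness in the safety comparison. If attribution did remove CT-arm events, there would also be some risk of understating a real difference.

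The size is unknown. The range of 0.75 to 7.5 patients among 150 rests entirely on an assumed rate of 0.5% to 5%, for which the documents give no source.

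**What to change.** 1. Keep the primary endpoint and its 90-day window. Add one sentence saying that GU and GI events within the window count regardless of attributed cause. Implant-related events that persist into the window then count, which should be said openly.
2. Widen the section Physician scored toxicity so that adverse events are recorded from allocation in both arms, including those from pre-SBRT procedures: fiducial placement and, where used, hydrogel spacer. Collect them at contacts already scheduled.
3. Report grade ≥2 GU, GI and infectious events from allocation to day 90 after SBRT, by assigned arm, as a secondary safety outcome.
4. Record whether the baseline toxicity and QOL assessment was taken before or after any implantation.

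The cost is a little more adverse-event recording, a flag on the baseline form and one extra table. Because Table 2 requires only one pre-treatment assessment, some pre-SBRT events would be collected by recall at the day-1 or 1-month contact, which is a modest loss of precision. No extra patients or procedures are needed, and the sample size is unchanged.

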### Patient-reported toxicity

The EPIC-26 questionnaire will be used to assess changes in the urinary incontinence, urinary obstruction, bowel, sexual function, and hormone/vitality domains [31]. Changes in domain scores at each time point will be classified as minimally important differences or not as previously reported [26].The IPSS questionnaire will be used to assess lower urinary tract symptoms [32]. Scores less than or equal to 7 indicate mild symptoms, scores ranging from 8 to 19 indicate moderate symptoms, and scores ranging from 20 to 35 indicate severe symptoms. A single question is included to inquire about the quality of life, and the answers range from “delighted” to “terrible” or from 0 to 6. Both changes in total IPSS scores from baseline and the total IPSS score at any given time point will be reported.The International Index of Erectile Function-5 (IIEF-5) or SHIM questionnaire will be used to assess erectile function [33]. The maximum score of 25 indicates maximal erectile function, while scores of 17 or lower indicate erectile dysfunction [34]. Both changes in total SHIM scores from baseline and the total SHIM score at any given time point will be reported.

### Treatment efficacy

Oncologic assessment for patients in this study will be consistent with patients managed with definitive radiotherapy for prostate cancer. This follow-up consists of PSA drawn every 3 months for the first year, then every 6 months until 5 years have passed since SBRT, and then once per year subsequently. Data of routine imaging (bone scan, CT or MRI) as clinically indicated will be collected on any patient who presents with any symptoms or PSA progression consistent with cancer recurrence. Recurrences will be managed according to the standard of care after primary radiotherapy for prostate cancer. Post treatment follow-up schedule is shown in Table 2.

**Table 2 Tab2:** Study calendar

Procedure	Pre Study	Pre-RT (up to 4 months prior)	Baseline Pre-SBRT Day 1	On Tx SBRT 5 fx	POST TREATMENT VISITS (+/− 4 weeks)*									
					1 month (+/− 4 wks)	3 month (+/− 4 wks)	6 month (+/− 4 wks)	9 month (+/− 4 wks)	12 month (+/− 4 wks)	18 month (+/− 4 wks)	24 month (+/− 4 wks)	Q 6 month × 4 yrs		EOS Or Early Term Visit
												30 M 36 M 42 M	48 M 54 M 60 M (+/− 4 wks)	
Informed Consent	x													
Demographics	x													
Medical History	x													
SOC Physical Exam	x													x
Toxicity assessments / Quality of Life Questionnaires		x**	x**		x	x	x	x	x	x	x	x		x
SOC Non-Contrast Pelvic CT scan^***^		x												
SOC MRI of the Prostate or Pelvis		x												
SOC PSA Draw****		x				x	x	x	x	x	x	x		x
Translational saliva collection◦			x											
Record Radiation Therapy - 5 fractions				x										

* Follow-up visits can be conducted over the telephone, with remote collection of QOL information

**Toxicity and QOL assessment required either at pre-RT OR pre-SBRT, but not at both time points

*** For patients with PSA < 1.0 ng/mL, the treatment planning CT can substitute for a diagnostic CT scan (in this case, the CT simulation should be within 1 month of radiotherapy initiation)

**** These SOC blood samples can be drawn remotely, in the event that the patient is following up outside the UCLA system. In these cases, the lab reports should be provided to the study investigators

◦ **Whenever feasible, but may be waived**

EOS, end of study; SOC, standard of care

### Data management and confidentiality

The radiation oncology research staff will be responsible for the database records of study patients. The data will be kept on the research coordinator’s computer, under password protection, with the patient information de-identified (study patients will be referred by their coded study number). A chart with all the relevant research patient information will be maintained for each patient by the research coordinator, and will be filed in a firewall protected computer. Only the research team (study coordinator, investigators, and project supporting staff) will have the password and key to the data from the study patients. Specimens will be stored under the patient’s coded study number. The patient’s name or other public identifiers will not be included in any information shared with other investigators. The master key that will identify specific study patients to their coded study number will be kept in a separate password protected file on the research coordinator’s computer. Only the study coordinator and the principal investigator will know the password to this file. Because SBRT is considered a standard of care option in the United States, no independent data monitoring committee is needed as there are no patient safety issues involved. The trial is subject to audit per the discretion of the IRB at the University of California, Los Angeles.

### Statistical analysis

#### Sample size

The PACE-B trial [4] and a multi-center SBRT trial run in the United States [14] provided the best estimate of acute grade ≥ 2 toxicities following modern SBRT. Extrapolating from these two trials, one would expect modern SBRT to have acute grade ≥ 2 GU and GI toxicity rates of 29.1 and 16.0%, and 5-year incidences of late grade ≥ 2 GU and GI toxicity of 13.3 and 2.0%. Based on a recently reported phase II study, MRI-guided SBRT may lead to acute grade ≥ 2 GU and GI toxicity rates of 19.8 and 3.0% [25]. Given that these results were based on an early MRI-guided SBRT experience and the PTV margin used in the MRI-guided arm in the current study is smaller (2 mm instead of 3 mm), it is reasonable to anticipate an acute grade ≥ 2 GU toxicity rate of closer to 15%.

The primary endpoint for this study is the incidence of acute grade ≥ 2 GU toxicity. The current study has been designed to detect a 14% reduction in acute toxicity, from 29 to 15%. An overall sample size of 300 patients (150 per arm) will provide 83.7% power to detect an absolute risk reduction of 14% with a one-sided, two-sample Z-test at a 0.025 significance level. Assuming an accrual of 75–100 patients per year, patients will be accrued over a period of 3.5 years and follow-up will continue for 5 years after the last subject is enrolled. However, the primary endpoint would be available for analysis 90 days after the final patient enrolled completes treatment. A trial designed to detect a smaller absolute difference in toxicity would be prohibitively large as for the expected difference, a trial of 300 patients is already required. Also given the cost of acquiring and operating an MRI-guided LINAC, one could also argue that a smaller absolute difference in toxicity would question the clinical relevance of the modality.

The study will also evaluate differences in the rate of acute grade ≥ 2 GI toxicity as well as the 5-year cumulative incidences of late grade ≥ 2 GU and GI toxicity. Other secondary endpoints include 5-year BCRFS (which will be stratified by risk group) and the proportion of fractions delivered that required online adaptation. Given the assumed toxicity rates, the absolute differences in the secondary toxicity endpoints that could be identified with 80% power, one-sided alpha 2.5% with *n* = 150 patients per arm are provided in Table 3.

**Table 3 Tab3:** Secondary endpoints power analysis

Secondary Endpoint	Assumed Rate in CT-Guided SBRT Arm	Absolute Difference at 80% Power (n = 150 per arm)
Acute grade ≥ 2 GI toxicity	16.0%	8.3%
Late grade ≥ 2 GU toxicity	13.3%	12.8%
Late grade ≥ 2 GI toxicity	2.0%	7.5%

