## Methods/design

This is a non-blinded single-center randomized trial designed to evaluate the superiority of MRI-guided SBRT over standard CT-guided SBRT for PCa in terms of acute physician-scored GU toxicity. Acute physician-scored GI toxicity, late physician-scored toxicity and patient-reported QOL, and five-year biochemical recurrence-free survival (BCRFS) will also be evaluated. We plan to enroll 300 patients with an expected rate of accrual in the range of 100 patients per year. Standard of care SBRT for localized PCa will be delivered either via an MRI-guided LINAC or a CT-guided LINAC. Five fractions of SBRT will be delivered within the span of 14 days (no more frequent than every other day), and patients will be followed for 5 years per routine standard of care. The trial schema is displayed in Fig. 1.

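### Table 3 does not give detectable reductions in toxicity: its two late rows are detectable increases, and its acute GI figure does not follow from the 16.0% printed beside it

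*Protocol article*

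**What the plan says.** The Methods/design section describes a trial "designed to evaluate the superiority of MRI-guided SBRT over standard CT-guided SBRT" in acute physician-scored GU toxicity; the other toxicity endpoints are evaluated alongside. The Abstract gives the aim more broadly, as finding out whether toxicity is lower after MRI-guided treatment.

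For the primary endpoint the Sample size section is explicit about direction. The trial is "designed to detect a 14% reduction in acute toxicity, from 29 to 15" per cent, and "An overall sample size of 300 patients (150 per arm) will provide 83.7% power to detect an absolute risk reduction of 14" per cent, "with a one-sided, two-sample Z-test at a 0.025 significance level".

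For the secondary endpoints the same section says that Table 3 provides, from the assumed toxicity rates, "the absolute differences in the secondary toxicity endpoints that could be identified with 80% power, one-sided alpha 2.5" per cent, again with 150 per arm. The table's rate column is headed "Assumed Rate in CT-Guided SBRT Arm". Its three rows are:

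- acute grade ≥ 2 GI: 16.0%, difference 8.3 points
- late grade ≥ 2 GU: 13.3%, difference 12.8 points
- late grade ≥ 2 GI: 2.0%, difference 7.5 points

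The direction of these differences is not stated. The text also cites a phase II study of MRI-guided SBRT with an acute GI rate of 3.0%.

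**The concern.** With a one-sided test, a CT-arm starting rate and a trial that looks for less toxicity, a reader will take the Table 3 figures as reductions from the CT rate. The late GI row fails that reading on sight, because a rate of 2.0% cannot fall by 7.5 points.

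The table is what a reader will use to judge what a null secondary result means. If it is wrong, the acute GI comparison looks better powered than it is and the late GU comparison looks worse. The late GI comparison is credited with 80% power when no possible reduction reaches it.

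**Working it through.** **Inputs** (all from the Sample size section and Table 3): n = 150 per arm; one-sided alpha 0.025, so z = 1.960; power 80%; CT rates 16.0%, 13.3% and 2.0%; two-sample Z-test; primary rates 29% and 15%; MRI phase II acute GI rate 3.0%.

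**Formula.** With rates p and q and mean m = (p + q)/2:

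- s0 = √[2m(1 − m)/n]
- s1 = √[(p(1 − p) + q(1 − q))/n]
- power = Φ[(|p − q| − 1.960·s0)/s1]

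**Step 1: reproduce the plan's own figure.** For 29% v 15%, m = 0.22, s0 = 0.04783 and s1 = 0.04715. Power = Φ[(0.14 − 0.09375)/0.04715] = Φ(0.981) = 83.67%. This is the protocol's 83.7%, so the test is identified as the Z-test with pooled null variance.

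**Step 2: solve for the difference that gives 80% power, in both directions.**

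| Row | Starting rate | Printed | Reduction | Increase |
|---|---|---|---|---|
| Acute GI | 16.0% | 8.3 | 10.07 (to 5.9%) | 13.51 |
| Late GU | 13.3% | 12.8 | 9.10 (to 4.2%) | 12.82 (to 26.1%) |
| Late GI | 2.0% | 7.5 | none | 7.50 (to 9.5%) |
| Check | 3.0% | – | none | 8.30 (to 11.3%) |

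The two late rows match the increase to the printed decimal. The acute GI row matches neither direction from 16.0%; it matches the increase from 3.0%.

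**Step 3: power of the printed figures read as reductions.**

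- *Acute GI, 16.0% to 7.7%.* m = 0.1185, s0 = 0.03732, s1 = 0.03701. Power = Φ[(0.083 − 0.07314)/0.03701] = Φ(0.266) = 60.5%. Reaching 80% would take 237 per arm.
- *Late GU, 13.3% to 0.5%.* m = 0.069, s0 = 0.02927, s1 = 0.02832. Power = Φ[(0.128 − 0.05736)/0.02832] = Φ(2.49) = 99.4%.
- *Late GI.* A 7.5-point fall is impossible. The largest possible fall, 2.0% to 0%, has m = 0.01, s0 = 0.01149, s1 = 0.01143. Power = Φ[(0.02 − 0.02252)/0.01143] = Φ(−0.220) = 41%. By one-sided Fisher's exact test, zero MRI events need at least 6 CT events (one-sided p is 0.030 with 5 and 0.015 with 6). The chance of 6 or more among 150 at 2.0% is 8%.

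**Step 4: sensitivity to the method.** Unpooled variance, pooled variance throughout, continuity correction and arcsine move the detectable reduction to 9.9–10.6 points for acute GI and 8.9–9.6 for late GU. For late GI at 0% the power ranges from 8% (Fisher) to 69% (arcsine), so it never reaches 80%. No row reproduces as a reduction under any of these, or at one-sided alpha 0.05 or 0.0125.

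**Step 5: sensitivity to follow-up.** The late figures treat 5-year incidence as a simple proportion in 150 fully followed patients per arm, as the table appears to do. If 120 per arm were evaluable (an illustrative assumption), the late GU reduction becomes 9.9 points.

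**The case against.** The strongest defence is that the table never says reduction. Its column is headed as an absolute difference, the text speaks of evaluating differences for secondary endpoints, and the superiority statement in Methods/design is tied to acute GU toxicity. On a neutral reading the two late rows are correct as detectable increases. That much stands: it would be wrong to infer that all three figures are unrelated to their CT rates, because only the acute GI figure is. The neutral reading does not rescue the table, however. The acute GI 8.3 fails in both directions, and a one-sided test for lower toxicity has no use for detectable increases.

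Three other inferences go further than the documents allow:

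- *That the trial cannot detect any late GI reduction.* Power is low but not zero; what can be said is that no reduction reaches 80%.
- *That the 3.0% rate was certainly the starting point for acute GI.* The match is to the printed decimal, but the article does not say so.
- *That the trial is undersized.* The sample size rests on the primary endpoint, and its stated power reproduces.

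It is also fair that the practical harm is limited. At the acute GI rates the article itself anticipates, 16.0% v 3.0%, s0 = 0.03386 and s1 = 0.03302, so power is Φ[(0.13 − 0.06636)/0.03302] = Φ(1.93) = 97%. The Discussion also concedes that a trial powered on late GU toxicity would be impractically large. No test, endpoint or stopping rule depends on Table 3.

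**Conclusion.** The point holds as an error in the secondary power statements. None of the three figures is the reduction detectable at 80% power, one-sided 2.5%, 150 per arm:

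- **Acute GI** is too favourable: 8.3 printed against about 10.1, with about 60% power at the printed value.
- **Late GU** is too unfavourable: 12.8 printed against about 9.1.
- **Late GI** is impossible as a reduction, and even complete elimination of events gives about 41% power by the Z-test and 8% by Fisher.

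These values rest on the article's CT-arm rates and on the Z-test that reproduces its primary power. For the late endpoints they also assume complete 5-year follow-up; losses would raise the late GU figure. The 3.0% origin of the acute GI entry is an inference. The primary calculation of 300 patients and 83.7% power is unaffected.

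**What to change.** Relabel the last column of Table 3 as the detectable absolute reduction. State beneath it the direction, the formula (two-sample Z-test, pooled null variance, one-sided 0.025, 80% power, 150 per arm) and, for the late rows, the assumption of complete 5-year follow-up. Enter:

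- acute GI: about 10.1 points (16.0% to 5.9%)
- late GU: about 9.1 points (13.3% to 4.2%), with a note that losses enlarge it, for example to about 9.9 with 120 evaluable per arm
- late GI: no reduction reaches 80% power (about 41% by the Z-test and 8% by Fisher even at 0%); report descriptively with a 95% confidence interval

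The cost is three table entries, one column label and a footnote. No patients, visits or procedures change.
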